**Sehemu D: Step 1: Uelewa kuhusu ugonjwa wa kisukari**

**Kumbuka**: Huuni utafiti, si mtihani. Majibu yako yatasaidia kutambua changamoto zilizopo katika jamii kuhusu ulaji bora. Kwa hiyo, kama hujui jibu, sema "sina na uhakika / Sijui" badala ya kubahatisha majibu.

| **Namba ya swali** | **Swali** | **Jibu** | **Code** |
| --- | --- | --- | --- |
| **Kisukari cha aina ya pili**: Vihatarishi, dalili, mikakati ya kuzuia, madhara ya kisukari, chakula bora, na magonjwa yasiyoambukiza yanayoambatana na ulaji usiozingatia afya. | | | |
| 37. | Umeishasikia kuhusu ugonjwa wa kisukari   1. Ndiyo 2.Hapana |  | Qn37 |
| 38. | **Kama jibu ni ndiyo, taja anagalau vihatarishi vitano vya ugonjwa wa kisukari.** |  |  |
|  | 1. Umri (Miaka 40 na kuendelea) |  | Qn38a |
|  | 1. Kutoshughulisha mwilia |  | Qn38b |
|  | 1. Kuongezeka sukari ndani ya damu |  | Qn38c |
|  | 1. Kuongezeka kwa mafuta kwenye damu |  | Qn38d |
|  | 1. Ulaji usiozingatia afya |  | Qn38e |
|  | 1. Historia ya kisukari ndani ya familia |  | Qn38f |
|  | 1. Shinikizo la damu la juu |  | Qn38g |
|  | 1. Unywaji wa pombe |  | Qn38h |
|  | 1. Uvutaji wa tumbaku |  | Qn38i |
|  | 1. Uzito wa juu |  | Qn38j |
|  | 1. Kuwa na kisukari wakati wa ujauzito |  | Qn38k |
|  | 1. Msongo wa mawazo |  | Qn38l |
|  | 1. Nyingine (taja)_______________________________ |  | Qn38m |
| 39. | **Taja angalau dalili 5 za kisukari** |  |  |
|  | 1. Njaa ya mara kwa mara |  | Qn39a |
|  | 1. Kiu ya mara kwa mara |  | Qn39b |
|  | 1. Kukojoa mara kwa mara hasa usiku |  | Qn39c |
|  | 1. Kupungua uzito ghafla |  | Qn39d |
|  | 1. Kutoona vizuri (upofu) |  | Qn39e |
|  | 1. Uchovu |  | Qn39f |
|  | 1. Midomo mikavu |  | Qn39g |
|  | 1. Ngozi kukauka na kuwasha |  | Qn39h |
|  | 1. Vidonda visivyopona haraka |  | Qn39i |
|  | 1. Others (specify)_______________________ |  | Qn39j |
| 40. | **Taja njia/mikakati 5 ya kuzuia ugongwa wa kisukari cha aina ya pili** | |  |
|  | 1. Kudhibiti uzito wa mwili |  | Qn39l |
|  | 1. Ulaji unaozingatia afya |  |  |
|  | 1. Kudhibiti shinikizo la damu |  | Qn40a |
|  | 1. Ulaji unaozingatia afya |  | Qn40b |
|  | 1. Kushughulisha mwili |  | Qn40c |
|  | 1. Kudhibiti kiwango cha sukari kwenye damu |  | Qn40d |
|  | 1. Kudhibiti kiwango cha mafuta kwenye damu |  | Qn40e |
|  | 1. Unywaji pombe unaozingatia afya |  | Qn40f |
|  | 1. Kuepuka msongo wa mawazo |  | Qn40g |
|  | 1. Kuacha kuvuta sigara |  | Qn40h |
|  | 1. Kutibu kiwango cha sukari wakati wa ujauzito |  | Qn40i |
|  | 1. Nyingine (taja)___________________________ |  | Qn40j |
| 41. | **Mention at least five complications of type2 diabetes** |  | Qn40k |
|  | 1. Kukatwa viuongo(miguu, mikono, vidole nk) |  | Qn40l |
|  | 1. Kiharusi (Stroke) |  |  |
|  | 1. Figo kushindwa kufanya kazi |  | Qn41a |
|  | 1. Upofu |  | Qn41b |
|  | 1. Kupungukiwa nguvu za kiume |  | Qn41c |
|  | 1. Uharibifu wa neva |  | Qn41d |
|  | 1. Shambulio la moyo |  | Qn41e |
|  | 1. Nyingine (taja)_____________________ |  | Qn41f |
| **Ubora wa chakula** | | | |
| 42. | Je! ni kiasi gani cha wanga, matunda, mboga mboga na protini kinachopaswa kuwa kwenye sahani ya chakula wakati wa ulaji kwa mtu anayezingatia afya?  1) ¼ ya wanga, ¼ ya protin, ½ matunda na mbogamboga, maji/maziwa  2)Sijui  3)Nyingine (taja)__________________ |  | Qn42 |
| 43. | Je! Unafikiri wataalamu wa afya wanashauri kwamba watu wanapaswa kula zaidi, kiasi sawa, au chini kwa vyakula vifuatavyo? (Tiki sanduku moja kwa kila chakula) |  |  |
|  | **Chakula** | **1.Zaidi**  **2.Kiasi saw**  **3.Kidogo**  **4.Sina hakika** |  |
|  | a) Mboga mboga |  | Qn43a |
|  | b) Vyakula vyenye sukari |  | Qn43b |
|  | c) Nyama nyekundu |  | Qn43c |
|  | d) Chakula cha wanga |  | Qn43d |
|  | e) Vyakula vyenye mafuta |  | Qn43e |
|  | f) Vyakula vyenye nyuzi |  | Qn43f |
|  | g) Matunda |  | Qn43g |
|  | h) Vyakula vyenye chumvi |  | Qn43h |
| 44. | Ni vipimo kiasi gani vya matunda na mboga mboga unafikiri vinashauriwa kuliwa na mtu kwa siku moja) (kipimo kimoja kinaweza kuwa chungwa moja au kiganja kimoja kilichojaa karoti zilizomenywa na kukatwakatwa)   1. Mtunda _______________ 2. Mbogamboga_______________ |  | Qn44 |
| 45. | Mafuta yaliyojaa sana hupatikana kwenye:  1.Mafuta ya mimea  2. Mafuta ya wanyama  3. Yote hapo juu  4. Sina uhakika |  | Qn45 |
| 46. | Ikiwa mtu antaka kupunguza kiasi cha chumvi katika chakula, ni nini chaguo bora kati ya haya yafuatayo? (chagua moja)  1. Kununua chakula ambacho tayari kimewekwa chunvi chumvi mfano sosegi, nyama za kopo, chipsi (clips) nk  2. Kuongeza chumvi mwenyewe wakati wa kupika  3. Sina uhakika |  | Qn46 |
| 47. | Je! Unafahamu magonjwa makubwa yasiyo ya kuambukizwa ambayo yanachochewa na kiasi kikubwa cha chumvi watu wanachokula?   1. Ndiyo 2. Hapana 3. Sina hakika |  | Qn47 |
| 48 | Ikiwa ndio, ni magonjwa gani yasiyotambulika unafikiri yanahusiana na chumvi?   1. Shinikizo la damu 2. Sijui 3. Nyingine (taja)______________________ |  | Qn48 |
| 49. | Je, unafahamu magonjwa yoyote yasiyo ya kuambukizwa yanayohusiana na ulaji mdogo wa matunda na mboga?   1. Ndiyo 2. Hapana 3. Sina hakika |  | Qn49 |
| 50 | Ikiwa ndio, ni magonjwa gani yasiyoyakuambukiza unafikiri yanahusiana na ulaji mdogo wa matunda na mboga?   1. Shinikizo la damu la juu 2. Kisukari 3. Kansa 4. Sijui 5. Nyingine (taja)______________________ |  | Qn50a  Qn50b  Qn50c  Qn50d  Qn50e |
| 51. | Je, unafahamu magonjwa yoyote yasiyo ya kuambukizwa yanayohusiana na kiasi cha mafuta watu wanayokula?  Ndiyo 2. Hapana 3. Sina hakika |  | Qn51 |
| 52. | Kama ndiyo, je ni magonjwa yapi yasiyoyakuambukiza yanahusiannishwa na ulaji wa mafuta mengi?   1. Shinikizo la damu la juu 2. Kisukari 3. Kansa 4. Sijui 5. Nyingine (taja)______________________ |  | Qn52a  Qn52b  Qn52c  Qn52d  Qn52e |
| 53. | Je, unafahamu magonjwa yoyote yasiyo ya kuambukizwa yanayohusiana na ulaji mdogo wa vyakula vyenye nyuzinyuzi?   1. Ndiyo 2. Hapana 3. Sina hakika |  | Qn53 |
| 54. | Kama ndiyo, je ni magonjwa yapi yasiyoyakuambukiza yanahusianishwa na ulaji mdogo wa vyakula vyenye nyuzinyuzi?   1. Shinikizo la damu la juu 2. Kisukari 3. Kansa 4. Sijui 5. Nyingine (taja)______________________ |  | Qn54a  Qn54b  Qn54c  Qn54d  Qn54e |
| 55. | Je, unafahamu magonjwa yoyote yasiyo ya kuambukizwa yanayohusiana unywaji wa pombe?  1.Ndiyo 2. Hapana 3. Sina hakika |  | Qn55 |
| 56. | Kama ndiyo, je ni magonjwa yapi yasiyoyakuambukiza yanahusianishwa na unywaji wa pombe?   1. Shinikizo la damu la juu 2. Kisukari 3. Kansa 4. Sijui 5. Nyingine (taja)______________________ |  | Qn56a  Qn56b  Qn56c  Qn56d  Qn56e |

**Sehemu E1: Upimaji wa Tabia – Utumiaji wa Tumbaku**

***Sasa nitakuuliza maswali yanayohusiana na tabia/mazoea mbalimbali yanayohusu afya. Haya yanahusisha masuala ya uvutaji sigara/tumbaku, unywaji wa pombe, ulaji wa matunda ma mbogamboga na mazoezi ya mwili. Tuanze na sigara/tumbaku.***

| **Namba ya swali** | **Swali** | **Jibu** | **Code** |
| --- | --- | --- | --- |
| 57. | Je, kwa sasa unavuta aina yoyote ya tumbaku kama vile sigara, kiko, sigara ya kusokota n.k? 1. Ndiyo 2. Hapana |  | Qn57 |
| 58. | **Kama Ndio,** Kwa sasa unavuta sigara au tumbaku **kila siku**? |  | Qn58 |
| 59. | Ulikuwa na umri gani ulipoanza kuvuta sigara kila siku kwa mara ya kwanza? __________________  Sijui: 77 |  | Qn59 |
| 60. | Unakumbuka ni muda gani uliopita?(JIBU MOJA TU)   1. Kwa miaka_______________________ 2. AU Kwa miezi______________ 3. AU Kwa wiki_____________ 4. Sikumbuki____________ |  | Qn60a  Qn60b  Qn60c  Qn60d |
| 61. | Kwa wastani, unavuta kiasi gani kwa siku cha kila moja ya aina zifuatazo za tumbaku? |  |  |
|  | 1. Sigara zinazotengenezwa viwandani __________ |  | Qn61a |
|  | 1. Sigara /tumbaku za kusokota kwa mikono __________ |  | Qn61b |
|  | 1. Kiko kilichojazwa tumbaku/sigara __________ |  | Qn61c |
|  | 1. Biri(Cigars)__________ |  | Qn61d |
|  | 1. Aina nyingine (taja)______________________________ |  | Qn61e |
| 62. | Hapo zamani, **ulishawahi** kuvuta sigara/tumbaku **kila siku**?  1. Ndiyo 2. Hapana |  | Qn62 |
| 63. | **Kama Ndio**, ulikuwa na miaka mingapi **ulipoacha** kuvuta sigara/tumbaku **kila siku**? |  | Qn63 |
| 64. | **Ni muda gani umepita** tangu ulipoacha kuvuta sigara/tumbaku kila siku? *(JIBU MOJA TU)*   1. Kwa miaka_______________________ 2. AU Kwa miezi______________ 3. AU Kwa wiki_____________ 4. Sikumbuki____________ |  | Qn64a  Qn64b  Qn64c  Qn64d |
| 65 | Kwa sasa unatumia aina yoyote ya tumbaku isiyo ya kuvuta kama vile ugoro, ‘kuber’ n.k.?  1. Ndiyo 2. Hapana |  | Qn65 |
| 66. | Ndani ya siku saba zilizopita, ni siku ngapi mtu mnayeishi naye ndani ya nyumba amevuta sigara ukiwepo?  1. Ndiyo 2. Hapana |  | Qn66 |
| 67. | Ndani ya siku saba zilizopita, ni siku ngapi mtu amevuta sigara kwenye eneo lisilo la wazi kazini ukiwepo?  1. Ndiyo 2. Hapana |  | Qn67 |

**Sehemu E2: Taarifa za tabia– Utumiaji wa Pombe/Vileo**

***Maswali yafuatayo yanauliza kuhusu utumiaji wa pombe/Vileo***

| **Namba ya swali** | **Swali** | **Jibu** | **Code** |
| --- | --- | --- | --- |
| 68. | Je, umewahi kutumia kinywaji chenye kilevi (kama vile bia, mvinyo, pombe kali au pombe ya kienyeji) katika **miezi 12 iliyopita**?  *(TUMIA kadi ya kielelezo AU TOA MIFANO)*   1. Ndiyo 2.Hapana |  | Qn68 |
| 69. | Je umekunywa kinywaji chenye kilevi ndani ya miezi 12 iliyopita?   1. Ndiyo 2.Hapana |  | Qn69 |
| 70. | Katika miezi 12 iliyopita, ni mara ngapi umekunywa angalau kinywaji kimoja chenye kilevi?( MSOMEE MAJIBU, TUMIA kadi ya kielelezo)  1.Kila siku  2.Siku 5-6 kwa juma  3.Siku 1-4 kwa juma  4.Siku 1-3 kwa mwezi  6.Chini ya mara 1 kwa mwezi |  | Qn70 |
| 71 | Umetumia kinywaji chenye kilevi (kama vile bia, mvinyo, pombe kali au pombe ya kienyeji) katika **siku 30 zilizopita**? *(TUMIA kadi ya kielelezo AU TOA MIFANO)*   1. Ndiyo 2.Hapana |  | Qn71 |
| 72. | Katika **siku 30** zilizopita, **ni mara ngapi** umekunywa angalau kinywaji kimoja chenye kilevi?  Idadi______________Sikumbuki (77) |  | Qn72 |
| 73. | Katika siku 30 zilizopita, ulipokunywa kinywaji chenye kilevi, kwa makisio ulikunywa vinywaji vingapi (standard drinks) kwa mkupuo  (*TUMIA KADI YA KIELELEZO)*  Idadi______________Sikumbuki (77) |  | Qn73 |
| 74. | Katika siku 30 zilizopita , ulipokunywa kinywaji chenye kilevi , ni kiasi gani **kikubwa** ulichokunywa (standard drink) siku uliyokunywa zaidi kwenye mkupuo mmoja ukijumlisha vinywaji vyote? |  | Qn74 |
| 75. | Katika siku 30 zilizopita, ni mara ngapi umekunywa Kinywaji chenye kilevi (standard drink);   1. **Kwa wanaume**: 5 au zaidi _______ 2. **Kwa wanawake**: 4 au zaidi _______   Kwenye mkupuo mmoja? |  | Qn75 |

**Sehemu E3: Taarifa za tabia– Lishe**

***Maswali yafuatayo yanauliza kuhusu matunda na mbogamboga ambazo unakula mara kwa mara. Hapa nina kadi ya maelezo ya lishe yenye mifano ya matunda na mbogamboga zinazopatikana katika maeneo yako. Kila picha inawakilisha kipimo kimoja. Unapojibu maswali haya tafadhali fikiria wiki moja ya kawaida katika mwaka uliopita***

| **Namba ya swali** | **Swali** | **Jibu** | **Code** |
| --- | --- | --- | --- |
| 76. | Kwa kawaida ni siku ngapi ndani ya wiki moja unakula **matunda**? *(TUMIA SHOWCARD*)  Idadi ya siku_____________Sifahamu (77) |  | Qn76 |
| 77. | Unakula matunda kipimo gani katika moja ya siku hizo? *(TUMIA SHOWCARD)*  Idadi ya siku_____________Sifahamu (77) |  | Qn77 |
| 78. | Kwa kawaida ni siku ngapi ndani ya wiki moja unakula **mbogamboga**? *(TUMIA SHOWCARD*)  Idadi ya siku_____________Sifahamu (77) |  | Qn78 |
| 79. | Unakula mbogamboga kipimo gani katika moja ya siku hizo? *(TUMIA SHOWCARD)*  Idadi ya siku_____________Sifahamu (77) |  | Qn79 |
| 80. | Ni aina gani ya **mafuta ya kupikia chakula** ambayo mnatumia mara kwa mara katika kaya yenu?   1. Mafuta ya wanyama 2. Mafuta ya mimea 3. Mafuta mchanganyiko 4. Sifuhamu |  | Qn80 |
| 81. | Kwa wastani huwa unakula milo mingapi kwa wiki ambayo haijaandaliwa nyumbani? Mlo hapa ni kifungua kinywa, mlo wa mchana na ule wa jioni?  Idadi ya siku_____________Sifahamu (77) |  | Qn81 |
| 82. | Je huwa unaongeza chumvi kwenye chakula kama haijakolea vizuri?   1. Hapana 2. Ndiyo |  | Qn82 |

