2.6 Material and method for each specific objective: A tool for data collection have been adopted from WHO STEP Survey questionnaire and other studies on similar topic(14,45–51). This tool will be then translated from English to Swhaili version. A tool also will consist of information including socio-demographic, behavioural, physical measurements and biological tests. A total of three focus group discussion (FGDs) involving street food vendors and six in-depth interviews with key stake holders will be conducted to assess their level of knowledge on type2 diabetes and hypertension risk factors and factors associated with adoption of food plate model and education package. Eight in-depth interviews will be conducted among public staff responsible with setting enabling and regulating working environment of food vendors. A three days training will be made to research assistants, this will involves orienting them on the study protocol, data collection tools and study ethics. **Table 3** shows the inclusion and exclusion criteria.

Table 3 Inclusion and exclusion criteria

| **Type of respondent** | **Inclusion** | **Exclusion** |
| --- | --- | --- |
| Street Food consumers | 1. Consuming at least three lunches meals/week to the same street food vendor (SFV) 2. Willing to participate in the study 3. Will remain in the study area for the duration of at least six months 4. Aged 25-64 years | Pregnant or lactating mothers |
| Street food vendors | 1. Vending food in the current site for not less than 6 months 2. Has at least 10 clients who have been consuming a least three lunch meals per week for not less than three months 3. Ready to implement the components required for an intervention model 4. Will remain vending food at same site for not less than six months 5. Aged 18 and above years | Not providing services daily |

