2.6.1 Magnitude of type2 diabetes, behaviourial and its risk factors: The prevalence of type 2 diabetes among urban street cooked food consumers will be determined. A person will be considered to have diabetes if the reading for fasting blood glucose measured using Accu-check machine is >7.0mmol/L or is on medication for raised blood glucose. This study will also assess the prevalence metabolic and behavioural risk factors of type 2 diabetes. Prevalence of metabolic risk factors will be assessed as follow: being overweight or obese (BIM≥25Kg/M^2^), raised TC (≥5.1mmol/L), raised TG (≥2 mmol/L), low HDL (<1.03 mmol/l for Male and < 1.29 for Female), raised LDL (>2.6 mmol/L), Abnormal Waist Hips Ratio for male and female if the value is >0.8 and >0.9 respectively, raised Systolic BP (≥140mmHg) and Diastolic BP (≥90 mmHg) (17,18). Behaviorial assessement will including participating in physical activities as per recommended standard (≥600MET/week), Behaviourial assessment will include consumption of fruits and vegetables as per standard (≥5 days per week), non-harmful drinking (5 or less for male and 4 or less for female units of alcohol per week) and not consuming table salt will be assessed (18,52).

**Blood Pressure (BP) Measurements**: Blood pressure will be measured while patients are in a sitting position, using an M4 Omron® device. An average of the last two readings taken three times consistently after three minutes from the left arm will be treated as final reading and will be used during analysis(18). The final will be classified as raised blood pressure if BP of ≥140/90mmHg.

**Weight Measurement**: SECA® weighing scale will be used to measure weight. Participant will be asked to remove any heavy clothing (such as coats and shoes) and stand still on the weighing scale, with hands by their sides.

**Height Measurement:** Height will be measured with a SECA® stadiometer, while a patient is facing directly ahead. Patients will be instructed to remove their shoes, caps or head scarf, keep their feet together, and stand with their arms by the sides. Measurement will be taken with heels, buttocks and upper back in contact with the stadiometer.

**Body Mass Index (BMI):** The product of weight (in Kilograms) divided by height squared (m^2^) will give BMI. Categorization BMI will be as follows ; obesity is ≥30 kg/m2; Overweight if the BMI is > 25 but < 30kg/m2, and normal if the BMI is between 18-25kg/m2 and underweight if below 19 kg/m^2^ (53).

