| 1. Body Mass Index or Waist Circumference 2. Fasting Blood Glucose 3. High Density Lipoprotein 4. Triglyceride 5. Systolic BP 6. Diastolic BP | **Socio-economic and demographic risks:**  Marital status, Education, Ethnicity, Employment status, Sex and Age  **Lifestyle behaviours**  Family history of diabetes  Smoking: Never/previously/currently; Frequency of smoking  **Physical activities**  Interview methods will be used in measuring:  Type, frequency and intensity, Work-related, communing and leisure physical activities  **Dietary pattern:**  Vegetables, Fruits, Spreads and oil, Table salt & Alcohol consumption  **Others factors:**  Mean number of health plate consumed per week,  Type2 diabetes knowledge of vendors and consumers |

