**Section D: Step 1: Attitudes towards living healthy life to prevent type2 diabetes**

| **Q-Number** | **Question** | **Response** | **Code** |
| --- | --- | --- | --- |
|  | **Statements** | 1.Strogly agree  2.Agree  3.Disagree  4.Strongly disagree |  |
| 22. | It is possible to prevent diabetes by dietary management |  | Qn22 |
| 23. | Family history of diabetes influences to follow disciplined life |  | Qn23 |
| 24. | Obesity increases the risk of diabetes |  | Qn24 |
| 25. | Regular exercise needs lots of effort |  | Qn25 |
| 26. | Everybody should be aware regarding prevention of diabetes with increasing age |  | Qn26 |
| 27. | If there is increased chance of getting diabetes e.g. having family history then there is nothing to do to prevent or delay occurrences of the disease. |  | Qn27 |
| 28. | If you try you can reduce the risk of diabetes |  | Qn28 |
| 29. | People who take steps to reduce the risk factors of diabetes, their possibility of occurring diabetes is less |  | Qn29 |
| 30. | You have little control on your health risk |  | Qn30 |
| 31. | If a person is rich and fat if the suddenly becomes thin and slender is a sign of running bankrupt |  | Qn31 |
| 32. | If somebody is fat has to maintain his/her body structure otherwise can be considered to be HIV positive |  | Qn32 |
| 33. | To become thin and slender is not good because people will consider one to be HIV positive |  | Qn33 |
| 34. | A glass of unsweeted juice is better than chewing the actual fruits |  | Qn34 |
| 35. | It is very difficult to yourself to avoind overfeeding if delicious foods are prently available |  | Qn35 |
| 36. | If salt is low teste low in foods it is better to add when you are eating in order to maintan the food teste |  | Qn36 |

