**Section E3: Step 1: Behavioural Measurements –Diet**

***The next questions ask about the fruits and vegetables that you usually eat. I have a nutrition card here that shows you some examples of local fruits and vegetables. Each picture represents the size of a serving. As you answer these questions please think of a typical week in the last year.***

| **Q-Number** | **Question** | **Response** | **Code** |
| --- | --- | --- | --- |
| 76. | In a typical week, on how many days do you **eat fruit**? *If Zero days, skip*  Number of days____________________Don't Know 77 |  | Qn76 |
| 77. | How many **servings** of fruit do you eat on **one** of those days? (*USE SHOWCARD) If Zero days, skip*  Number of days___________________Don't Know 77 |  | Qn77 |
| 78. | In a typical week, on how many days do you **eat vegetables**?*(USE SHOWCARD) If Zero days, skip*  Number of days___________________Don't Know 77 |  | Qn78 |
| 79. | How many **servings** of vegetables do you eat on one of those days? *(USE SHOWCARD) If Zero days, skip*  Number of days____________________Don't Know 77 |  | Qn79 |
| 80. | What type of **oil or fat is most often** used for meal preparation in your household?*(USE SHOWCARD)* *(SELECT ONLY ONE)*   1. Animal Oil 2. Vegetable oil 3. Both(mixed) 4. DK |  | Qn80 |
| 81. | On average, how many meals per week do you eat that were not prepared at a home? By meal, I mean breakfast, lunch and dinner.  Number of days____________________Don't Know 77 |  | Qn81 |
| 82. | Do you add salt when you eating some food?   1. Yes 2. No |  | Qn82 |

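### Swahili Qn82 asks about adding salt to under-seasoned food and drops the reference to eating, so the tool's only table-salt item does not match its English source

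*Protocol*

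**What the plan says.** The English questionnaire (Appendix B, Section E3, Qn82) asks "Do you add salt when you eating some food", with 1 for yes and 2 for no. The Swahili questionnaire (Appendix B, Sehemu E3, Qn82) asks "Je huwa unaongeza chumvi kwenye chakula kama haijakolea vizuri", with the answers listed as "1. Hapana 2. Ndiyo", so 1 is no and 2 is yes. Both rows carry the variable name Qn82.

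Section 2.6 sets out how the two forms are related: "This tool will be then translated from English to Swhaili version".

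The item has two stated uses. Section 2.6.1 lists it among the behaviours to be measured: "not consuming table salt will be assessed". Table 4 lists dietary predictors for the joint model as "Vegetables, Fruits, Spreads and oil, Table salt & Alcohol consumption", and systolic and diastolic blood pressure are among the dependent variables.

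**The concern.** A translated item should ask the same question as its source. Here two elements of meaning changed. The phrase *kama haijakolea vizuri* makes the question conditional on the food being under-seasoned. The words for when eating have gone, so salt added during cooking is no longer excluded.

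No other item supplies the missing information. Qn36 is an attitude statement and Qn43h and Qn46 to Qn48 test knowledge. If Qn82 records something other than adding salt at the table, both the descriptive estimate in Section 2.6.1 and the Table 4 predictor rest on the wrong quantity. Analysis cannot recover it, because nothing else in the tool shows which yes answers depended on the condition.

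**Working it through.** **No figure to reproduce.** The Protocol gives no prevalence of table-salt use, no validation of the item and no estimate of how its wording shifts answers. The check is therefore mainly textual.

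**Comparing the two forms of Qn82**

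| Element | English | Swahili |
| --- | --- | --- |
| Condition | none | only if the food is not well seasoned |
| Occasion | when eating | not stated |
| Usual practice | present tense, no frequency | *huwa*, usual practice, no frequency |
| Code 1 / code 2 | yes / no | no / yes |

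The missing phrase was available to the translator. Swahili Qn36 (Sehemu D) contains *wakati wa kula*. The under-salted condition also appears in English Qn36, which says of low-salt food that "it is better to add when you are eating in order to maintan the food teste". The Swahili behaviour item has thus moved towards that attitude item, although it remains a yes/no report of the respondent's own practice.

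**Expected direction.** Someone who regularly salts food at the table can be expected to say yes to either form. Someone who adds salt only to bland food, or only while cooking, might say no to the English form but yes to the Swahili one. The extra error is then mainly false positives.

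**What such an error would do, under assumed values only.** Let p be the true share of table-salt users and q the share of the others who say yes. Assume that every true user says yes, that the error does not depend on the outcome, and that those wrongly counted have the same mean outcome as other non-users. Then:

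- recorded prevalence = p + (1 − p)q
- share of the unadjusted mean difference retained = p / [p + (1 − p)q]

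Neither p nor q comes from the Protocol. Each cell shows recorded prevalence, then the share retained:

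| p | q = 0 | q = 10% | q = 30% | q = 50% |
| --- | --- | --- | --- | --- |
| 10% | 10%, 100% | 19%, 53% | 37%, 27% | 55%, 18% |
| 20% | 20%, 100% | 28%, 71% | 44%, 45% | 60%, 33% |
| 30% | 30%, 100% | 37%, 81% | 51%, 59% | 65%, 46% |
| 50% | 50%, 100% | 55%, 91% | 65%, 77% | 75%, 67% |

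For example, at p = 20% and q = 10%: 0.20 + 0.80 × 0.10 = 0.28, and 0.20 / 0.28 = 0.71. The table runs from no effect to a large one, so it cannot settle the size.

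**The answer codes are a separate fault.** If Swahili answers were read with the English key, a recorded 28% would become 72% and the sign of the coefficient would reverse. That is inversion, not dilution. Correcting the codes would leave the wording fault in place.

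**The case against.** The strongest reply is that the Swahili answer may often be right. Section 2.6.1 refers to not consuming table salt, which is any use against none, and sets no standard of habitual use. A person who salts bland food at the table does consume table salt. The English item has no frequency of its own, so occasional adders may say yes to both forms. *Huwa* already asks about usual practice, so the Swahili item is not purely hypothetical. All of this stands, and it is why the bias could be close to zero.

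Two things limit the reply. The introduction to Section E3, in both languages, asks respondents to think of a typical week, although it is written about fruit and vegetables. A person who rarely salts can answer no on that basis, whereas a conditional question sidesteps it. The reply also does not cover salt added in cooking, which the Swahili wording lets in.

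A reader might infer more than the documents support:

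- **That most yes answers come from people without the habit, or that a salt–blood pressure association would vanish.** This needs assumed prevalences and a habitual-use standard that the Protocol does not contain. In a multivariable joint model even the direction of the bias is not guaranteed.
- **That the item would hide an effect of the health education.** Sections 2.7.1 and 2.7.2 do not name salt among the education or plate-model content, and Section 2.6.4 does not list salt use among the comparisons between arms.

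It is also not established that the Swahili text in Appendix B is the final field version, since Section 2.6 speaks of translation as still to come. It is nevertheless the Swahili text the Protocol contains.

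**Conclusion.** The mismatch holds. Swahili Qn82 does not ask the question in its English source, and it is the only measure of a behaviour named in Section 2.6.1 and of a predictor named in Table 4. The likely direction is a higher recorded prevalence and a weaker simple contrast between users and non-users. That rests on some respondents answering the two forms differently, on error unrelated to outcome, and on an unadjusted comparison. The size is unknown and may be small; the illustrative percentages are not estimates for this trial.

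The reach is limited to one descriptive prevalence and one of many predictors. The primary outcomes, the listed arm comparisons and the sample size are unaffected. The point still deserves correction because the remedy is trivial before data collection and unavailable afterwards.

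**What to change.** In Appendix B, Sehemu E3, reword Qn82 to match the English: delete *kama haijakolea vizuri* and add *wakati wa kula*, for example *Je, huwa unaongeza chumvi kwenye chakula wakati wa kula?* In the same row, set the codes to 1 = Ndiyo and 2 = Hapana, as in the English form. Have the item back-translated before use, and use identical wording and codes at baseline and endline.

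The cost is one phrase and one code order in the Swahili form before printing, plus a short back-translation check. The new wording aligns the two forms but does not measure frequency of salting, since the English item does not either.
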